### Interventions

#### Training

The training will be based on the specialized low-intensity rehabilitation program, including exercise and respiratory therapy and mental gait training, which has been previously described [32, 35, 50, 51].

The initial phase of exercise training will be closely monitored, as it will be held in hospital for approximately 3 weeks period and later will be continued for further 12 weeks at home. In-hospital stays will be arranged country-specific, and hospitalization times may range. The rehabilitation program will comprise interval ergometer training (20 min 5 days per week), dumbbell training of single muscle groups (30 min 5 days a week), respiratory therapy (30 min 5 days per week), mental training and guided walks (individually, at least two times a week), and conventional elements, such as massages, relaxation, lectures, and patient education.

Individual training adjustment will be performed according to clinical assessments at baseline and follow-up and the patient’s subjective perception throughout the program. Training intensity will be started at 40–50% of the maximal patient’s workload, reached during the cardiopulmonary exercise test at baseline, and will be increased within the in-hospital period, trying to achieve the maximal baseline workload (maintaining 60–80% of the peak heart rate and avoiding desaturation < 90%). Overexertion must be strictly avoided. In order to ensure safety and adherence, every workout will be supervised by a physiotherapist during an in-hospital phase. Before leaving the hospital, each patient will receive individualized written recommendations on how to continue exercising at home. The patient will be asked to document daily trainings (intensity, duration, pulse rate, blood pressure, adverse events), which will be discussed at the follow-up visits.

#### Control

Patients in the control group will not receive exercise training and will continue their regular treatment and daily activities for 15 weeks. After 15 weeks, control group patients will be offered to take part in the exercise training program (waiting-group design). In this case, the final assessment of the patient in the control group will also serve as a baseline assessment for a participant in the training group.

### Individual withdrawal criteria

The patient will be withdrawn from the study at any time, if he/she wishes to discontinue or if one of the following occurs due to exercise training:➢Signs of acute heart failure➢Syncope➢Symptomatic ventricular tachycardia➢Worsening of WHO functional class

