### Assessments

#### Efficacy assessment

Efficacy parameters in both groups will be assessed at baseline and after 15 weeks (mean or median changes from baseline to 15 weeks, comparing changes within trained and control groups as well as mean/median changes between these groups). Patients in the training group will additionally perform the 6-MWD at the end of in-hospital rehabilitation.

The primary endpoint is to determine the effect of standardized exercise and respiratory training on exercise capacity, measured by the mean change of 6-MWD (baseline vs 15 weeks vs control group) in the HFpEF-PH population.

Secondary endpoints include mean/median changes from baseline to 15 weeks of echocardiography parameters, cardiopulmonary exercise testing, World Health Organization (WHO) functional class, measurement of safety parameters, health-related quality of life assessment (SF-36 questionnaire), anxiety and depression assessment (HADS scale), optional right heart catheterization at rest and during exercise, and optional cardiac magnetic resonance imaging (MRI). A detailed description of the evaluative parameters of each test is provided in the following paragraph (the “Procedures” section).

A follow-up interview will be performed by phone at the end of the study (last patient, last visit) to assess safety and compliance and observe survival. The long-term compliance and risk profile of exercise training will be explored to identify risk factors and record adverse events.

The detailed timeline of the study is shown in Fig. 1.

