#### Statistical analysis

The data from all centers will be pooled. If sample sizes allow, center effects on the primary and secondary outcomes will be analyzed.

Descriptive statistics will be displayed by treatment and control groups corrected for the active treatment group, including the usual location and scale statistics (mean, median, standard deviation, standard error, first and third quartiles, minimum, and maximum) and 95% confidence limits of the mean and median. Frequency tables for qualitative data will be provided. As an unbalanced distribution of baseline characteristics may not be completely excluded, baseline clinical parameters including patient risks and prognostic implications will be analyzed and compared between the groups.

The primary efficacy analysis will be based on an analysis of variance with the baseline values as a covariate (ANCOVA). This analysis provides a power advantage over the standard two-sided Student’s *t*-test leading to a statistical power of 85% or more. If the preconditions for ANCOVA are not met, a *t*-test with robust variance estimation (Welch test) will be used. Secondary endpoints will be analyzed by comparison of the mean changes between baseline and 15 weeks in the two groups (training vs control group) adjusted for the baseline value (ANCOVA or Wilcoxon rank sum test for non-parametric data). Categorical data will be analyzed by the McNemar test or chi-square test as appropriate. Exploratory data analysis of follow-up will be conducted by descriptive statistics and comparing baseline values and follow-up examinations. In case of ≤ 20% of missing values of a variable, a multiple imputation strategy will be used and analyzed as sensitivity analysis for data interpretation. The primary analysis set is the intention-to-treat analysis population (all patients randomized into the study). As a sensitivity analysis, the per-protocol population will be analyzed (all patients actually taking part in the study). Patients not fulfilling the inclusion criteria will be excluded in a separate sensitivity analysis using the per-protocol set.

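### Withdrawing patients from the study, rather than from training, for training-related events can remove poor week-15 outcomes from the training arm and tilt the comparison in its favour

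*Protocol article*

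**What the plan says.** Protocol article, Individual withdrawal criteria: a patient is to be "withdrawn from the study at any time, if he/she wishes to discontinue or if one of the following occurs due to exercise training". Four events follow: signs of acute heart failure, syncope, symptomatic ventricular tachycardia, and "Worsening of WHO functional class". What the patient leaves is the study. The article nowhere says that a withdrawn patient still attends the week-15 visit (V4).

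Other sections bear on this rule:

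- **Control:** "Patients in the control group will not receive exercise training" for the 15 weeks; the programme is offered to them only afterwards.
- **Efficacy assessment:** "Efficacy parameters in both groups will be assessed at baseline and after 15 weeks". The secondary endpoints, also changes to week 15, include "World Health Organization (WHO) functional class, measurement of safety parameters".
- **Statistical analysis:** "The primary efficacy analysis will be based on an analysis of variance with the baseline values as a covariate (ANCOVA"), and "The primary analysis set is the intention-to-treat analysis population (all patients randomized into the study"). Multiple imputation is a sensitivity analysis, used when no more than 20% of a variable is missing. In a further sensitivity analysis "the per-protocol population will be analyzed (all patients actually taking part in the study").
- **Risks assessment:** adverse events are recorded for the whole trial. Efficacy assessment adds a phone interview at the end of the study on safety, compliance and survival.

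**The concern.** Read together, these sections make loss of the week-15 outcome depend on both arm and outcome. A control patient cannot have an event caused by training during the comparison period. A control who develops acute heart failure or drops a WHO class therefore stays in and contributes a week-15 value. A trained patient with the same event, if it is attributed to training, leaves.

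The WHO-class trigger is the clearest case, because worsening is both a secondary endpoint and a reason for removal. The primary endpoint is exposed to the extent that patients with these events would have walked less far at week 15.

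At stake is whether the primary analysis compares the arms as randomized, or compares trained patients who tolerated the programme with nearly all controls. The error would favour training, and it cannot be repaired once the week-15 visit has been missed.

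**Working it through.** **Inputs.** From Sample size calculation: difference 35 m, SD of the change 50 m, two-sided alpha 0.05, power 85%, 38 per group, 15% dropout, 45 per group. The documents give no rate of training-related withdrawal, so the counts below (2, 4 or 7 of 45) are assumptions. Seven of 45 is 15.6%, about the whole planned dropout allowance (0.15 × 45 = 6.75).

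**1. The plan's own figure.** The exact two-sample t-test power is 84.4% at 37 per group and 85.3% at 38, so 38 is right. Then 38 / 0.85 = 44.7, rounded up to 45. The sample size reproduces.

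**2. General formula for the bias.** If a share f of the training arm is removed and its mean change lies x metres below the full-arm mean, the observed arm mean rises by f·x / (1 − f). With x = 50 m (1 SD):

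- f = 5%: 0.05 × 50 / 0.95 = +2.6 m
- f = 10%: 0.10 × 50 / 0.90 = +5.6 m
- f = 15%: 0.15 × 50 / 0.85 = +8.8 m

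**3. Upper bound.** If those removed are exactly the worst share f of a normal distribution, the bias is 50·φ(z_f) / (1 − f), where z_f is the f-quantile and φ the standard normal density. This gives +5.4, +9.7 and +13.7 m at 5%, 10% and 15%.

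**4. Effect on the test.** 20,000 simulated trials under no true effect, with 45 per arm, changes normal with SD 50 m, k trained patients removed, all controls kept, and a t-test on those remaining. In the moderate case, removal follows a latent score correlated 0.5 with the 6-MWD change.

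| Removed (k of 45) | Bias, correlation 0.5 | Two-sided type I error | Bias, exactly the worst | Two-sided type I error |
|---|---|---|---|---|
| 2 | +2.4 m | 5.9% | +4.7 m | 8.3% |
| 4 | +4.2 m | 7.2% | +8.5 m | 14.5% |
| 7 | +6.9 m | 10.1% | +13.8 m | 28.4% |

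A repeat simulation of the moderate case gave +2.3, +4.4 and +6.8 m with 5.8%, 7.2% and 9.4%, so the last type I error is best read as 9–10%. As a cross-check, a correlation of 0.5 should halve the upper bound: 0.5 × 4.7 = 2.35, 0.5 × 8.5 = 4.25 and 0.5 × 13.8 = 6.9 m.

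False claims in favour of training, nominally 2.5%, are 4.4%, 6.2% and 9.6% in the moderate case and 7.4%, 14.1% and 28.3% at the bound. Most of the errors therefore point one way.

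**5. Against the planned effect.** The moderate biases are 2.4/35 = 7%, 4.2/35 = 12% and 6.9/35 = 20% of the planned 35 m. The bounds are 4.7/35 = 13%, 8.5/35 = 24% and 13.8/35 = 39%.

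**Simplification.** The simulation tests the change without the baseline covariate of the planned ANCOVA.

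**The case against.** Several points against the concern are sound and limit it.

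- **Safety.** A reader might infer that safety is censored at the very events of interest. The documents do not support this. The triggering event falls under adverse-event recording, trainees log adverse events with each session, and the closing phone interview covers safety and survival. What can be lost is the week-15 safety parameters and possibly later events.
- **Intention to treat.** A reader might infer that the withdrawal rule contradicts the analysis set. It does not: the set is defined by randomization, and a missing outcome leaves that definition intact. The rule defeats the purpose of the set in practice.
- **One-sidedness.** Withdrawal at the patient's own wish applies to both arms, and a trained patient whose deterioration is judged unrelated to training stays in. Only the four event triggers are one-sided.
- **WHO class.** Worsening first recognised at V4 is captured at V4. The loss concerns worsening acted on earlier.
- **Size.** The upper bound requires those withdrawn to be exactly the poorest walkers, which syncope or tachycardia need not identify. Seven withdrawals would use up about the whole dropout allowance on training-related events in a low-intensity programme.
- **Remedies in the plan.** Missing data are queried back to the centres, trainees have an extra 6-MWD at the end of the in-hospital phase, and imputation is planned. But a query cannot produce a test that was not done, the extra test is not a week-15 value and has no control counterpart, and standard imputation assumes missingness at random, which this rule makes implausible.
- **Condensed text.** The full protocol may keep withdrawn patients in follow-up, and the bias would then largely vanish. The article, however, states an explicit rule that points the other way, so the sentence would still need correcting.

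**Conclusion.** The concern stands in this form: the rule as written joins stopping training to leaving the study, and its event triggers can act in only one arm of the randomized comparison. The training arm can therefore lack week-15 6-MWD, WHO-class and safety-parameter values for patients who did badly on training. Neither the intention-to-treat label nor imputation confined to a sensitivity analysis repairs that.

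The direction, in favour of training, assumes that withdrawn patients would have walked less far at week 15. This is plausible given the triggers but is not shown in the documents. The size is conditional on the assumed counts: small for one or two withdrawals, material at around 10–15% of the arm. The moderate scenario (about +2 to +7 m, two-sided type I error about 6% to 10%) is the fairer guide. The range up to about +14 m and 28% is a ceiling and should not be read as an expected bias.

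**What to change.** Amend Individual withdrawal criteria so that discontinuing training and leaving the study are separate. Possible wording: *If one of the listed events occurs, training is discontinued. The patient remains in the study unless consent is withdrawn. Week-15 (V4) outcomes, at least 6-MWD and WHO class, are sought where the treating physician considers testing permissible, and safety follow-up continues.*

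In Statistical analysis, state that these patients are analysed in the arm to which they were randomized, with their observed week-15 values. Some values will not be obtainable, so add a sensitivity analysis that assumes worse outcomes for training-arm patients with a missing week-15 value. One way is to lower their imputed 6-MWD by a range of shifts and report the shift at which the conclusion changes.

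The clinical criteria for stopping training are left as they are, and no view is taken on them. The sample size stays at 90 and V4 is already scheduled. The cost is an amendment, some effort to bring back patients who have stopped training, and one additional analysis.

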### Data collection and management

Each center will receive study-specific case record forms (CRF) to collect the data and enhance data integrity. Information obtained will be pseudonymized. The rules of medical confidentiality and data protection will be followed.

The data will be prospectively collected in every participating center. All findings including clinical and laboratory data will be documented in the patient’s medical record. The center’s principal investigator will be responsible for the patients’ safety, study conduct, and data quality, ensuring that all sections of the database are completed correctly and entries can be verified against source data. The biometrician and trial coordinator, appointed by Thoraxklinik at Heidelberg University Hospital (Core center of the study), will be able to access all (e)CRFs and check for reliability, consistency, and completeness of the data. Based on these checks, queries will be produced combined with the queries generated by visual control. All missing data or inconsistencies will be reported back to the respective recruiting center and will be followed upon completion.

### Assessments

#### Efficacy assessment

Efficacy parameters in both groups will be assessed at baseline and after 15 weeks (mean or median changes from baseline to 15 weeks, comparing changes within trained and control groups as well as mean/median changes between these groups). Patients in the training group will additionally perform the 6-MWD at the end of in-hospital rehabilitation.

The primary endpoint is to determine the effect of standardized exercise and respiratory training on exercise capacity, measured by the mean change of 6-MWD (baseline vs 15 weeks vs control group) in the HFpEF-PH population.

Secondary endpoints include mean/median changes from baseline to 15 weeks of echocardiography parameters, cardiopulmonary exercise testing, World Health Organization (WHO) functional class, measurement of safety parameters, health-related quality of life assessment (SF-36 questionnaire), anxiety and depression assessment (HADS scale), optional right heart catheterization at rest and during exercise, and optional cardiac magnetic resonance imaging (MRI). A detailed description of the evaluative parameters of each test is provided in the following paragraph (the “Procedures” section).

A follow-up interview will be performed by phone at the end of the study (last patient, last visit) to assess safety and compliance and observe survival. The long-term compliance and risk profile of exercise training will be explored to identify risk factors and record adverse events.

The detailed timeline of the study is shown in Fig. 1.

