Patient characteristics and efficacy parameters (secondary and exploratory endpoints) will be analyzed at baseline and 15 weeks. The values for each respective group will be displayed as mean ± standard deviation or mean ± standard error of the mean. Changes from baseline to 15 weeks will be analyzed by robust Student’s *t*-test (Welch test). Frequency data will be displayed as *n* and %. This data will be analyzed by the chi-square test and McNemar test. By means of correlation and regression analysis, the influence of different factors on the training effect will be investigated. *P*-values < 0.05 will be considered significant.

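### Within-arm change stands beside the between-arm contrast as an efficacy comparison under one P < 0.05 rule, and the two analysis paragraphs disagree on the test for secondary changes

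*Protocol article*

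**What the plan says.** All places are in the protocol article.

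- **Efficacy assessment.** Efficacy parameters are measured at baseline and week 15, "comparing changes within trained and control groups as well as mean/median changes between these groups". The two comparisons are not ranked. The primary endpoint is worded as exercise capacity "measured by the mean change of 6-MWD (baseline vs 15 weeks vs control group) in the HFpEF-PH population", which runs the time contrast and the control contrast together.
- **Statistical analysis, main paragraph.** "The primary efficacy analysis will be based on an analysis of variance with the baseline values as a covariate (ANCOVA"), with a Welch test as fallback. "Secondary endpoints will be analyzed by comparison of the mean changes between baseline and 15 weeks in the two groups (training vs control group"). This comparison takes baseline into account through ANCOVA, or uses a Wilcoxon rank sum test where the data are non-parametric. On categorical outcomes the text reads: "Categorical data will be analyzed by the McNemar test or chi-square test as appropriate".
- **Statistical analysis, last paragraph, on patient characteristics and on secondary and exploratory endpoints.** "Changes from baseline to 15 weeks will be analyzed by robust Student"'s t-test, identified there as the Welch test; the contrast is not named and no baseline adjustment is mentioned. Chi-square and McNemar are named again for frequency data. The section closes with the rule that P-"values < 0.05 will be considered significant", which is not limited to between-arm tests.

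**The concern.** A change from baseline within one arm mixes any training effect with everything else that moves over 15 weeks: familiarity with the walk test, regression to the mean, and the diuretic changes that the article permits. The randomised control arm is there to remove what the arms share. A within-arm p-value removes none of it.

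The usual misreading is to test each arm separately, find the training arm significant and the control arm not, and conclude that training works. That conclusion has no controlled error rate, because it depends on the size of the shared change. The text leaves this route open: within-arm comparison is listed as part of efficacy, a paired test is named, and a single significance threshold applies throughout. The exposure lies in the secondary endpoints, of which there are many. WHO functional class is the clearest case, because it is categorical and so falls under the McNemar or chi-square wording.

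A second problem sits in the same text. The two analysis paragraphs do not give the same method for changes in secondary endpoints.

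**Working it through.** **1. The plan's own figure.** Inputs from Sample size calculation: difference 35 m, SD of the change 50 m, 38 per arm, two-sided alpha 0.05, 15% dropout.

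- Standard error of the difference = 50 × √(2/38) = 11.47 m.
- Noncentrality = 35/11.47 = 3.05 on 74 degrees of freedom. The noncentral t distribution gives 85.3% power, matching the stated 85%.
- 38/(1 − 0.15) = 44.7, rounded up to 45 per arm, or 90 in total, as stated.

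The sizing is therefore a between-arm calculation, and it reproduces.

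**2. How often the misleading pattern arises.** From the article: 38 per arm and SD of change 50 m. Assumed: the same true gain m in both arms, so that training has no effect, and a two-sided 5% paired t-test in each arm. The article gives no value for m, so a range is shown.

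- Standard error of one arm's mean change = 50/√38 = 8.11 m; critical t on 37 degrees of freedom = 2.026.
- p(m) = probability that one arm shows a significant gain, from the noncentral t with noncentrality m/8.11.
- The arms are independent and share the same m, so the probability of a significant gain in training but not in control is p(1 − p).

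| Shared true gain m | Noncentrality | p: training gain significant | p(1 − p): training significant, control not |
|---|---|---|---|
| 0 m | 0 | 2.5% | 2.4% |
| 5 m | 0.62 | 8.7% | 7.9% |
| 10 m | 1.23 | 22% | 17% |
| 15 m | 1.85 | 44% | 25% |
| 20 m | 2.47 | 67% | 22% |
| 30 m | 3.70 | 95% | 5% |

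The product p(1 − p) cannot exceed 25%, which it reaches at p = 0.5. A 15 m gain is close to that peak. At larger gains the pattern becomes rarer because both arms turn significant. A simulation of 200,000 trials at 0, 10, 15, 20 and 30 m agreed with these values. The between-arm test stayed at about 5% two-sided at every shared gain, that is 2.5% for a false benefit of training.

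These figures use the walk-distance SD because it is the only SD in the article. Walk distance itself is protected by the primary ANCOVA. The table shows how the mechanism behaves at this sample size; it is not an error rate for WHO class or any other secondary endpoint.

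**3. The two analysis paragraphs side by side.** The main paragraph analyses secondary endpoints between arms with adjustment for baseline. The last paragraph analyses changes from baseline to week 15, for secondary and exploratory endpoints, by a Welch test. Welch compares two independent samples, so the natural reading is change scores compared between arms, unadjusted. On that reading each continuous secondary endpoint has two different analyses, and the article does not say which one governs.

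**4. McNemar.** The test needs paired binary data. The arms are randomised in parallel and are not matched, so the only natural pairing is baseline with week 15 in the same patients. Its use here is therefore within an arm.

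**The case against.** The strongest reply is that the inferential rules are in Statistical analysis, and there both the primary and the secondary analyses are training against control, adjusted for baseline. The phrase in Efficacy assessment is a parenthesis about measurement; it names no test and no decision rule. This stands. A reader might infer that efficacy as a whole is to be judged by within-arm tests, or that the primary conclusion is exposed. The article supports neither, and the sample size also rests on the two-sample comparison.

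A reader might also take the Welch sentence as an unpaired test of baseline against week-15 values inside an arm. The article does not say so, and the between-arm reading is the more natural one. Such a test would also have too large a standard error and make within-arm significance rarer, so the criticism cannot be added to the percentages above, which require paired tests.

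It is fair, too, that the shared gain is an assumption and that the pattern is uncommon at both ends of the range. The full range is shown for that reason. Confounding by diuretic changes is limited by the requirement of optimised therapy, stable for at least one month before entry, although later diuretic changes remain permitted.

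Finally, a condensed article may leave detail to the full protocol or analysis plan. That does not dispose of the point, because what is at issue is stated text: the within-arm comparison, McNemar, the unrestricted threshold, and a Welch sentence at odds with the paragraph before it.

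**Conclusion.** A minor point of wording and consistency that should be corrected. The primary ANCOVA and the sample size are unaffected. What stands is that within-arm change is listed as an efficacy comparison without descriptive-only status, that a paired test is named for categorical data, that one significance threshold covers all tests, and that the Welch sentence, read between arms, contradicts the baseline-adjusted analysis of secondary endpoints.

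With paired tests, 38 per arm, an SD of change of 50 m and an equal true gain in both arms, the false pattern ranges from about 2% with no shared gain to a peak near 25% at 15 m, and back to 5% at 30 m. The corresponding false between-arm benefit is 2.5% throughout. The size of the shared gain is assumed, and the figures are illustrative for the secondary endpoints. The inconsistency between the two analysis paragraphs depends on no assumed figure.

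**What to change.** 1. **Efficacy assessment:** state that within-arm change is descriptive only, shown as the mean paired change with its 95% confidence interval and no p-value. State that every efficacy statement rests on the baseline-adjusted difference between arms, and word the primary endpoint as that difference.
2. **Statistical analysis, both paragraphs:** replace McNemar as an efficacy test with a between-arm comparison of the categorical outcome.
3. **Statistical analysis, last paragraph:** replace the Welch sentence with the baseline-adjusted between-arm analysis already given in the main paragraph (ANCOVA, or Wilcoxon for non-parametric data). The Welch fallback for the primary analysis is not affected.
4. **Significance rule:** tie the P < 0.05 threshold to between-arm comparisons.

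The cost is wording only. No patients, visits or data are added and the sample size does not change. The within-arm p-values are given up.
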